## Abstract

**Background:**

The aging population is associated with increased multimorbidity and polypharmacy. Older adults are at a higher risk of adverse events and reduced therapeutic response. This phenomenon is partially explained by drug interactions and treatment adherence. Most randomized clinical trials have found no significant differences between morning and evening levothyroxine (LT_4_) administration in young adults, but there is little evidence regarding alternative LT_4_ regimens in older populations. Thus, the MONIALE trial aims to test an alternative schedule for LT_4_ administration in older adults.

**Methods/design:**

This randomized crossover clinical trial will include participants aged 60 years or older with primary hypothyroidism. The trial groups will consist of morning LT_4_ intake (60 min before breakfast) or evening LT_4_ intake (60 min after supper). The primary outcome will be variation in serum thyrotropin (TSH) levels after 24 weeks of the LT_4_ protocol. The secondary outcomes will be the prevalence of drugs that potentially interact with LT_4_ and hypothyroidism control according to interaction status. The sample size was calculated to detect a minimum mean difference of 1 mUI/L in serum TSH level between the groups with 80% power and a 5% probability of type I error, resulting in 91 patients per group. The project was approved by the Hospital de Clínicas de Porto Alegre Ethics Committee.

**Discussion:**

Considering the aging population, the increased prevalence of multimorbidity and polypharmacy, as well as potential drug interactions and treatment adherence difficulties, an alternative LT_4_ protocol could be useful for hypothyroidism treatment in the elderly. Prior studies comparing alternative LT4 administration protocols have mainly included young adult populations and have not addressed potential drug interactions.

**Trial registration:**

ClinicalTrials.gov, NCT03614988. Registered 30 July 2018.

## Background

Epidemiologic and demographic changes have resulted in aging of the population [1]. Between 1980 and 2017 the number of people aged 60 years or older worldwide has risen from 362 to 982 million, and by 2050 people in this age range will outnumber those in all other age ranges [2].

Older age is associated with a higher prevalence of multiple chronic diseases [3, 4] and polypharmacy, which is generally defined in the literature as the use of five or more concomitant medications [5]. Adverse events, such as drug–drug interactions [6], non-adherence [7], suboptimal therapeutic effectiveness, and poor clinical response [8] are related to multiple drug use. Both multimorbidity and polypharmacy are correlated with falls, hospitalizations, functional limitations, and mortality [9, 10].

The prevalence of thyroid dysfunction increases with age [11, 12]. The National Health and Nutrition Examination Survey, conducted between 1988 and 1994, found a hypothyroidism prevalence of 4.6% (0.3% clinical and 4.3% subclinical), being more common in women aged between 50 and 70 years (*p* < 0.001) [12]. Physiological changes due to the aging process could impact hypothyroidism treatment [13]. In older populations, pharmacokinetics might be modified by gastrointestinal aging and decreases in body water content, serum albumin, hepatic biotransformation, and renal clearance [14].

Levothyroxine is a synthetic derivative (levorotatory isomer) of thyroxine. Its ionization state and dissolution are influenced by gastric pH [15]. Although in healthy volunteers bioavailability can reach 60–80% [16, 17], there could be a 9.4% decrease in thyroxine absorption in patients over 70 years old (62.8% ± 13.5% SD vs 69.3% ± 11.9%; *p* < 0.001), as was found in a study of 45 euthyroid individuals [18]. The small bowel is the main site of absorption; the duodenum accounts for 15 ± 5% SD, the upper jejunoileum 29 ± 14% SD, and the lower jejunoileum 24 ± 11% SD of 24-h ^131^I-labeled thyroxine absorption [16]. The time necessary to reach the maximum serum concentration (Tmax) of the drug is approximately 2–3 h from ingestion, and plateaus occur at 18 and 48 h. Food and hypothyroidism delay Tmax [19, 20].

Drug bioavailability is responsible for most inter- and intra-individual therapeutic variation [6], which can result from (a) nonadherence, (b) physiological (weight, pregnancy, age) and paraphysiological (behavior, nutrition) conditions, (c) malabsorption diseases, and (d) concomitant medications [8].

In an in vitro study, Pabla et al. found that a higher pH impairs dissolution of thyroxine [21], and Centanni et al. observed a higher thyroxine requirement in ten euthyroid patients with multinodular goiter who were receiving concomitant omeprazole [22]. In a prospective study, however, the hormone levels of 19 hypothyroid subjects did not change when they were advised to take omeprazole 30 min after LT_4_ [23]. Besides the known interaction with proton pump inhibitors, interactions between LT_4_ and other drugs/supplements have been recognized [24], such as with iron [25], calcium supplements [26], aluminum hydroxide [27], raloxifene [28], sevelamer [29], cholestyramine [30], and ciprofloxacin [31]. In light of these findings, the American Thyroid Association recommends a 4-h interval between potentially interfering drugs, although this is based on a low grade of evidence [32].

A survey of referral centers about the appropriate use of LT_4_ revealed that, although the majority of patients understood that LT_4_ should not be taken with food, only 52.1% were aware that it should also not be taken with other medications [33]. Forgetting to take the tablets and a lack of understanding about the need for continued treatment were found to be the causes of low adherence in two-thirds of 100 uncontrolled hypothyroidism patients [34].

In 1977, in a sample of healthy volunteers, Wenzel and Kirschsieper found that LT_4_ absorption decreased from 79.3% ± 7.2% SD under fasting conditions to 63.9% ± 10.5% SD after a meal of two buttered rolls and a boiled egg (*p* < 0.001) [17]. Years later, Bevenga et al. demonstrated that postponing breakfast from 15 to 20 min to 60 min improved the thyroid function tests in hypothyroid individuals [20]. LT_4_ has also been reported to interact with coffee [35], soy [36], grapefruit [37], and milk [38].

Although some prospective studies on the timing of LT_4_ administration have been published, they were not designed to include older adults. In a pilot study, Bolk et al. [39] assessed the TSH levels of 19 hypothyroid women (mean age 48 years) for 24 h on two separate days. Evening LT_4_ intake (hours after supper) lowered TSH levels more than morning intake (30 min before breakfast) (1.2 ± 0.3 mUI/L vs 5.1 ± 0.9 mUI/L, *p* < 0.01). Despite the bedtime LT_4_ regimen, the circadian pattern of thyrotropin was maintained and did not interfere with morning blood sampling [39]. The same group was able to reproduce these results in a randomized crossover placebo-controlled trial with 90 hypothyroid patients (mean age 48 years), who were followed for 24 weeks. In the intergroup comparison, bedtime intake had a direct treatment effect, with a decrease in TSH levels of 1.25 mIU/L (95% confidence interval (CI) 0.60–1.89 mIU/L; *p* = 0.001) and an increase in free T4 of 0.07 ng/dL (95% CI 0.02–0.13, *p* = 0.01) compared to intake 30 min before breakfast [40]. Rajput et al. [41] randomized 152 drug-naive hypothyroidism patients (mean age 34.30 ± 11.82 years) into two parallel groups to receive LT_4_ 2 h after dinner or 30 min before breakfast. At the end of 12 weeks, finding no significant difference between treatment strategies for both euthyroidism (96% vs 90%; *p* = 0,19) and mean serum TSH levels (3.27 mUI/L ± 4.19 vs 5.13 mUI/L ± 9.36; *p* = 0.31) [41]. Bach-Huynh et al. evaluated three timing strategies in 65 patients (48 ± 13 years) and found that taking LT_4_ an hour before breakfast resulted in significantly lower TSH levels (1.06 mIU/L 95% CI 0.60–1.52 mIU/L; *p* < 0.001) than when taking it 20 min before breakfast or 2 h after supper [42]. In agreement with these results, Perez et al. found higher serum TSH levels when LT_4_ was taken at the beginning of breakfast (2.89 mIU/L ± 2.82 vs 1.9 mIU/L ± 1.76; *p* = 0.028) than when taken 1 h before [43]. A recent study obtained data from 84 patients (71% aged ≤ 65 years old) on stable doses of LT_4_. They performed a three-period crossover trial of LT_4_ administration (30 min before breakfast, 1 h before lunch and 2 h after supper). No significant differences in thyroid profile results were found in the per-protocol analysis [44].

### Trial rationale

Most published studies on the timing of LT_4_ administration have analyzed young populations and have not addressed the use of intervening medications. This trial aims to test an alternative schedule for LT_4_ administration in older adults with a randomized crossover clinical trial. Morning administration, which is more commonly used, will be compared with evening administration for 3 months of follow-up. This report follows the SPIRIT Statement guidelines [45]. We present a standardized checklist with recommended SPIRIT Statement items (Additional file 1).

## Methods/design

### Study design and setting

This prospective, randomized crossover trial will be conducted at the Endocrinology and Internal Medicine Clinic at the Hospital Clínicas de Porto Alegre, Brazil.

### Eligible participants

The research team will identify outpatients ≥ 60 years old with primary hypothyroidism who have been using LT_4_ for at least 6 months and have been on stable doses for the last 3 months. The study procedures will be explained to those who meet the inclusion criteria, and those who provide written informed consent will be enrolled. Screening will continue until the target population is achieved.

### Exclusion criteria

The exclusion criteria are severe organic syndrome, dementia, thyroid cancer, heart failure (functional class IV), or three or more hospital admissions in the last year due to heart failure decompensation, and refusal to participate.

### Intervention

Participants will be instructed to take LT_4_ tablets according to random treatment allocation, either in the evening (60 min after supper) or in the morning (60 min before breakfast). After 3 months of follow-up, the treatment will be changed using a crossover strategy.

### Outcomes

#### Primary outcome

Change in serum TSH levels after 24 weeks of follow-up.

#### Secondary outcomes

To identify concomitant drugs that affect LT_4_ absorptionTo compare TSH control efficacy between the two treatment strategies according to age, drug interaction, and sex subgroups

### Sample size calculation

SAS Studio 3.7 was used to calculate the sample size. The calculated sample size (182 participants, 91 in each group) can detect a difference of 1.0 mUI/L between the means as significant, considering a standard deviation of 2.0 for group 1 and 3.87 for group 2 (BOLK, 2010). A power of 80% and significance level of 5% were considered in the calculation. Adding 10% for possible losses and refusals, the sample size should be 200.

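### The stated 182 participants (91 per group) with 80% power for 1.0 mUI/L does not follow from the protocol's own inputs; for the planned crossover the error is conservative and the paragraph needs restating

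*Protocol article*

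**What the plan says.** The section on sample size calculation gives both the inputs and the result. The result is: "The calculated sample size (182 participants, 91 in each group) can detect a difference of" 1.0 mUI/L in mean TSH. The variability is given by "considering a standard deviation of 2.0 for group 1 and 3.87 for group 2", with an earlier trial as the source. The error rates are given as follows: "A power of 80% and significance level of 5% were considered in the calculation". Ten percent is then added for losses, giving 200. The abstract repeats the per-group count: "resulting in 91 patients per group".

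The design is not a two-group comparison. Under Intervention, after three months "the treatment will be changed using a crossover strategy", so every participant takes LT4 on both schedules. The section on statistical methods names an ANOVA for 2 × 2 crossover studies as the analysis of the treatment effect. The Background describes earlier evidence of the same type, "in a randomized crossover placebo-controlled trial with 90 hypothyroid patients", with a difference of 1.25 mIU/L (95% CI 0.60 to 1.89).

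**The concern.** The sample size paragraph uses the language of two independent groups: a group 1, a group 2, one SD for each, and a number in each. The trial compares two schedules within the same patients. These are different calculations. The first needs the two SDs alone; the second needs the SD of the within-patient difference, which depends on how strongly a patient's two TSH values are correlated.

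All the ingredients of an independent-groups calculation are printed, so its result can be checked, and 91 per group does not come out. If the stated power is wrong, readers will judge a null or a positive result against a figure that does not describe the trial. They also cannot tell whether 91 was meant as the whole trial or as one sequence.

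**Working it through.** **Inputs (Sample size calculation):** difference d = 1.0; SDs s1 = 2.0 and s2 = 3.87; power 80%; significance 5%. Sidedness is not stated, so two-sided is assumed. Sum of variances: 2.0² + 3.87² = 4.000 + 14.977 = 18.977.

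**Step 1. Try to reproduce 91 per group as independent groups.** n per group = (1.960 + 0.842)² × (s1² + s2²) / d² = 7.849 × 18.977 = 148.9, so 149. The unequal-variance noncentral t gives 151 per group. At 91 per group the power is 58.5% (t) or 59.1% (normal approximation). The difference detectable with 80% power is √(18.977 × 7.849 / 91) = 1.28 mUI/L, not 1.0.

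Other conventions do not rescue the figure:
- One-sided 5%: 118 per group.
- Simple average of the two SDs: 136 two-sided, 107 one-sided.
- SD 2.0 alone (two-sided): 63.
- SD 3.87 alone (two-sided): 236.

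**Step 2. The planned crossover.** Each patient contributes a difference with variance SD_d² = s1² + s2² − 2ρ·s1·s2 = 18.977 − 15.48ρ. Total N and power come from the noncentral t on those differences. The detectable difference at N = 182 is approximately 2.80 × SD_d / √182; the table gives the t-based value. The article does not state ρ, so a range is shown.

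| ρ (assumed) | SD_d | Total N for 80% power | Power with 182 | Difference detectable at 80% with 182 |
|---|---|---|---|---|
| 0 | 4.36 | 151 | 86.9% | 0.91 |
| 0.3 | 3.79 | 115 | 94.4% | 0.79 |
| 0.5 | 3.35 | 91 | 98.0% | 0.70 |
| 0.6 | 3.11 | 78 | 99.1% | 0.65 |

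Using N − 2 instead of N − 1 degrees of freedom changes only the last total, to 79. For 182 to be the total that gives 80% power, ρ would have to be about −0.25.

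**Step 3. Where 91 may come from.** At ρ = 0.5, 91 pairs give 80.4% power and 91 is the smallest total reaching 80%. That suggests a paired calculation whose answer was then applied to each sequence.

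**Step 4. A check from the article's own background.** The cited crossover's CI gives SE = (1.89 − 0.60) / (2 × 1.99) = 0.324. If about 90 patients were analysed, SD_d = 0.324 × √90 ≈ 3.1. Setting 18.977 − 15.48ρ equal to 3.08² gives ρ ≈ 0.61, close to the last row of the table.

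**The case against.** The strongest defence is that the planned analysis is the crossover ANOVA. With 182 patients it has at least 87% power at every non-negative correlation, so the promise of 80% is kept. That stands, and it sets the severity: the error is conservative. The extra patients also help the planned age, sex and drug-interaction comparisons. It is also fair that a journal article may leave the correlation to a fuller document, so its absence alone is not the point. The point is that the article prints inputs and a result that do not agree.

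A reader might infer four stronger things, none of which the documents support:
- *That the trial is underpowered at 58%.* That figure belongs to a comparison of two independent groups. The brief primary-outcome line (change in TSH after 24 weeks) could be read that way on its own, but the section on statistical methods fixes the crossover analysis.
- *That 91 is shown to have been double counted.* The value 0.5 appears nowhere in the article; it was found because it returns 91. A one-sided calculation with ρ near 0.3 gives almost the same total (90), so the match is suggestive, not proof.
- *That enrolment should be cut to 91.* With 91 patients power is 80% at ρ = 0.5, but 70% at 0.3 and 58% at 0. The support from the cited crossover assumes that about 90 patients were analysed and that variability at mean age 48 carries over to patients aged 60 or older.
- *That the loss allowance is wrong.* Adding 10% to 182 gives 182 × 1.10 = 200.2, which is what the article says it did. Dividing by 0.9 would give 203, a negligible difference here.

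**Conclusion.** Wrong as written, of moderate severity. The statement that 182 participants, 91 per group, give 80% power for 1.0 mUI/L is not obtained from the stated inputs as independent groups under any convention tried. For the crossover it would need a negative correlation of about −0.25. The mismatch is large as a description (58% on the wording used, 87% to 99% on the design planned for correlations 0 to 0.6), but the primary comparison is not endangered.

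The independent-groups result rests only on the printed inputs and a two-sided test. The crossover figures rest in addition on the assumed correlation, and 98% power in particular holds only at 0.5. That 182 exceeds the crossover requirement does not depend on that choice, provided the correlation is not negative.

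**What to change.** Keep 182 evaluable and 200 enrolled, and rewrite the paragraph for the 2 × 2 crossover:

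1. State the assumed SD of the within-patient **differences** (3.35 at correlation 0.5, or about 3.1 if about 90 patients were analysed in the cited crossover), or state the correlation. Label it as the SD of differences. The residual within-patient SD of the crossover ANOVA is smaller by √2 (3.35 / 1.414 = 2.37). Entering 3.35 as that residual SD would give 179 patients and 81% power at 182, and so hide the problem.
2. Say whether 91 is a total or a per-sequence number, and whether the test is two-sided.
3. Restate the power for 1.0 mUI/L as about 98% at correlation 0.5 (range 87% to 99% for correlations 0 to 0.6). Alternatively, give the difference detectable with 80% power as about 0.7 mUI/L (range about 0.65 to 0.91).
4. Correct the abstract's per-group sentence to match.

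The cost is wording in two places. No additional patients are needed, and design and analysis stay as they are.

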### Random allocation

A randomization list stratified by sex was created using a web-based program (http://www.randomization.com/). An interchangeable random blocks/variable blocks randomization strategy was chosen to assure allocation concealment. An independent researcher is responsible for the randomization list and treatment allocation.

### Blinding

Due to the crossover design, the trial participants, staff, and outcome assessors will be not blinded, although data analysis will be blinded.

### Data collection methods

Eligible participants will attend meetings at 0, 12, and 24 weeks after enrollment. Each meeting will include application of standardized questionnaires to assess drug–food–thyroxine interactions, treatment adherence, and adverse events. Blood samples will be collected at baseline, 12 weeks, and 24 weeks after initial treatment allocation to measure free T4 and TSH levels. Figures 1 and 2 describe the follow-up procedure.

**Fig. 1 Fig1:**
[figure not shown]
Flow chart of the MONIALE trial: inclusion criteria, randomization, and follow-up process

**Fig. 2 Fig2:**
[figure not shown]
SPIRIT figure: Allocation, interventions and outcomes

Thyroid function (serum TSH and free T4 levels) will be measured by electrochemiluminescence assay; concentrations of 0.27–4.2 mUI/L and 0.93–1.7 ng/dL, respectively, are the method’s reference limits. Food–LT_4_ interactions will be analyzed according to time since last meal (< 30 min, 30–60 min, or > 60 min). Concomitant use (within 60 min) of calcium or iron supplements, proton pump inhibitors, other supplements/multivitamins, and daily medications will be considered in the drug–LT_4_ interaction assessment. The Morisky–Green test will be used to verify treatment adherence and comprehension at baseline and follow-up. Side effects will also be investigated regarding causality between LT_4_ treatment and severity. Patients will be discontinued from the allocated intervention upon individual request or worsening of their clinical condition due to decompensated hypothyroidism.

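### Food interaction is classified only by time since the last meal, so breakfast eaten too soon after a morning dose goes undetected while the matching evening lapse is caught

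*Protocol article*

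**What the plan says.** The Intervention section of the Protocol article tells participants to take levothyroxine "either in the evening (60 min after supper) or in the morning (60 min before breakfast"). Each regimen is thus tied to one meal, on opposite sides of the dose.

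The assessment text that follows Fig. 2, under Data collection methods, states that food "interactions will be analyzed according to time since last meal", in three bands: <30, 30–60 and >60 min. No other meal interval is given. The same paragraph sets the drug window without a direction: "Concomitant use (within 60 min) of calcium or iron supplements", among other products.

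The data come from visits at 0, 12 and 24 weeks, each with "application of standardized questionnaires to assess drug–food–thyroxine interactions, treatment adherence, and adverse events". The questionnaire items are not reproduced. Adherence has its own instrument: "The Morisky–Green test will be used to verify treatment adherence and comprehension at baseline and follow-up".

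The Background explains why the breakfast interval is of interest. It reports a study in which "postponing breakfast from 15 to 20 min to 60 min improved the thyroid function tests in hypothyroid individuals".

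**The concern.** The food measure and the morning instruction point in opposite directions. The measure counts from the previous meal to the dose, while the instruction "or in the morning (60 min before breakfast") concerns the time from the dose to the following meal. A lapse of the kind the Background links to thyroid function tests would leave no trace in the stated bands. The equivalent evening lapse would show up directly.

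What is at stake is the description of food interaction by regimen, and any later attempt to explain TSH results by it. If evening intake showed more food interaction than morning intake, nobody could tell whether behaviour differed or only one kind of lapse had been measured.

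**Working it through.** The plan gives no figure to reproduce on this point, so the check applies the stated bands to the stated regimens.

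**Inputs.** Bands: <30, 30–60 and >60 min since the last meal (Data collection methods, text after Fig. 2). Regimens: evening dose 60 min after supper, morning dose 60 min before breakfast (Intervention).

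**Step 1: classify typical doses.** For a dose taken before breakfast, the last meal is normally the previous evening's, hours earlier.

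| Dose | Interval the instruction concerns | Time since last meal | Band |
|---|---|---|---|
| Morning, breakfast 60 min later | 60 min forward | hours | >60 |
| Morning, breakfast 20 min later | 20 min forward | hours | >60 |
| Morning, breakfast 5 min later | 5 min forward | hours | >60 |
| Morning, taken during or shortly after breakfast | wrong order | minutes | <30 or 30–60 |
| Evening, 20 min after supper | 20 min back | 20 min | <30 |
| Evening, 45 min after supper | 45 min back | 45 min | 30–60 |
| Evening, exactly 60 min after supper | 60 min back | 60 min | 30–60 |

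The first three rows cannot be told apart. A morning dose in the wrong order is flagged. An early evening dose is flagged, and an evening dose taken exactly as instructed shares a band with the one at 45 min.

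**Step 2: size of the asymmetry.** Let *p* be the share of doses with less than 60 min between dose and meal, taken as equal in both regimens, with morning doses correctly ordered before breakfast.

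- Evening share detected: *p*
- Morning share detected: 0
- Apparent difference: *p* − 0 = *p*, although the true difference is 0

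The documents give no value for *p*. Over an assumed range of 10% to 50%, the spurious gap is 10 to 50 percentage points. Evening doses reported at exactly 60 min would add to the evening count if the 30–60 band were read as exposure to food.

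**Step 3: where the bands enter the analysis.**

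- Primary outcome: change in serum TSH (Outcomes). The bands are not part of it.
- Treatment effect: 2 × 2 crossover ANOVA, with outcomes presented by intention to treat (Statistical methods). No food term and no exclusion by meal timing is stated.
- Secondary comparison: subgroups by age, drug interaction and sex (Outcomes). Food interaction is not listed.
- Additional subgroup: age 60–74 versus ≥75 years (Statistical methods).

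The bands therefore have no stated route into the TSH comparison. They enter only the food-interaction assessment and whatever is built on it.

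**The case against.** The strongest reply is that this is loose wording in a condensed article. The questionnaire is not shown, it may well ask about the following meal, and the investigators evidently knew that the breakfast interval matters, since they defined the morning regimen by it. All of that may be true. However, the article does not leave the food variable open: it names the interval and the cut-points, and followed as written they give the asymmetric result above. If the wording is only shorthand, one sentence corrects it.

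Four stronger readings are tempting, and the documents do not support them.

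- A reader might infer that morning doses will always look acceptable. They will not: a morning dose taken during or after breakfast falls in the shorter bands. Only a correctly ordered dose followed too soon by breakfast is missed.
- A reader might infer that the two regimens are compared unfairly on efficacy. The TSH analysis uses neither the bands nor any exclusion based on them.
- A reader might take 30–60 min as a non-compliant class. The article labels no band that way and assesses adherence separately. The cut-point matter is only that exactly 60 min is grouped with earlier doses, and self-reported times are seldom exact to the minute.
- A reader might infer that completed visits lack the breakfast interval. That cannot be known without the questionnaire.

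It is also fair to say that no formal comparison of food-interaction rates between regimens is announced. The harm is thus to a descriptive variable and to possible explanatory use of it.

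**Conclusion.** The point holds in a limited form. As worded, the food classification cannot detect breakfast eaten too soon after a pre-breakfast dose, but it does detect an evening dose taken too soon after supper. An evening dose at exactly the instructed interval also shares a band with earlier ones. Food-interaction rates by regimen would be ascertained asymmetrically, in favour of the morning regimen.

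With equal true lapse rates, the artefact equals the lapse rate itself. The 10 to 50 points shown rest on an assumed range, but the direction does not depend on it. The conclusion assumes that the wording is applied literally and that the last meal before a pre-breakfast dose is normally that of the evening before. It reads the abstract's reference to interaction status as drug interaction, as the Outcomes section has it. The primary TSH comparison is not affected through this variable.

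**What to change.** Define the food interval as the time from the dose to the nearest meal, before or after. At weeks 0, 12 and 24, record both minutes since the last meal and minutes to the next meal, if the questionnaire does not already do so. Classify on the shorter of the two, with bands <30, 30–59 and ≥60 min, so that the interval named in the Intervention section falls in the top band under either regimen. This changes the measurement only; the instructions to participants stay as they are.

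The cost is at most one added questionnaire item and a moved cut-point. The Trial status section says recruitment began in May 2018, so some visits may already be complete. If the item was not asked at those visits, report the interval to the next meal as missing for them, and do not infer it from time since the last meal. If the questionnaire already records both intervals, only the sentence defining the classification needs to change.
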